## Synopsis

The primary objective of the PENELOPE study is to assess the prevalence of unmet target LDL-C (1.8 mMol/L) despite a standardized stepwise high intensity lipid modifying therapy in patients with ASCVD and at very high risk for recurrent events.

Consecutive patients presenting with a type I (N)STEMI and a history of ASCVD and/or Diabetes mellitus II will be included. Prevalence will be determined of unmet target LDL-C (1.8 mMol/L) at each therapeutic step (Baseline, high intensity statin therapy (HIST) , HIST+ ezetimibe, HIST + ezetimibe + PCSK9-I), and after one year of therapy.

## Sample size calculation

The sample size is calculated to provide a prevalence (LDL>1.8 mMol/L in patients mentioned in the primary objective) with 95% confidence interval with a width (upper bound minus lower bound) of 5%.

The prevalence of LDL-C >1.8 mMol/L in patients treated with high-intensity statin and ezetimibe (~ primary objective) is estimated at 0.20 based on the IMPROVE-IT study. Seventy five percent of patients on simvastatin and ezetimibe in the IMPROVE-IT study have a LDL < 62 mg/dL (1.6 mMol/L). Since a higher threshold (1.8 mMol/L) and more potent statins are used in the current study, the prevalence is estimated at 20%. Using this assumption, 983 patients are needed to ensure a 95% confidence interval with a width of 5% (margin of error: 2.5%). The number is rounded up to 1000 patients.

$$\text{Sample size (n)} = \frac{Z^2 \times p \times (1 - p)}{d^2}$$

Where Z= 1.96 (confidence interval 95 %), d= margin of error of 0.025 %, prevalence (p) = 0.2

$$\frac{1.96^2 \times 0.2 \times 0.8}{0.025^2} = 983$$

## Primary Endpoint

prevalence of an LDL-C >1.8 mMol/L in a subgroup of very high risk patients, despite guideline based therapy with HIST and/or ezetimibe

## Secondary Objective(s):

- Prevalence of an LDL-C >1.8 mMol/L in patients with a medical history of ASCVD and/or T2DM and presenting with a new type I (N)STEMI, with or without lipid modifying therapy.
- Prevalence of an LDL-C >1.8 mMol/L in patients as described in a.) after 4 weeks of HIST (i.e., atorvastatin  $\geq 40$  mg or rosuvastatin  $\geq 20$  mg; or the documented highest tolerated dose of a statin).
- Prevalence of an LDL-C >1.8 mMol/L in patients as described in the primary objective after 4 weeks of HIST + ezetimibe 10 mg + alirocumab 75 Q2W or 150 mg Q2W.
- Prevalence of an LDL-C >1.8 mMol/L after 1 year of follow up.
- Adherence to lipid modifying therapy after 1 year
- Prevalence of drug-related adverse events of the lipid modifying drugs and a subgroup analysis between male/ female and >70y and  $\leq 70$ y.

g) Prevalence of discontinuation of the lipid modifying drugs and a subgroup analysis between male/ female and  $>70y$  and  $\leq 70y$ .

h) Major adverse cardiovascular events (Myocardial infarction, stroke, (re-)hospitalization for cardiovascular diseases, revascularization and cardiovascular death) after 1 year

## Statistical analysis

Statistical analysis will be descriptive only. The study is intended nor powered to perform intergroup analysis.

The prevalence of the patients not reaching the target level at baseline will be calculated by dividing the proportion of patients with LDL-C  $> 1.8$  mMol/L at baseline by the total included patients.

For each consecutive step the net and the cumulative effect will be calculated. The net effect is the percentage of patients who reach the target (LDL-C  $\leq 1.8$  mMol/L) in the corresponding step. The cumulative effect is the percentage of all patients who reach the target (LDL-C  $\leq 1.8$  mMol/L) in the previous and the current steps. The labelling of the groups and the calculation of the net and cumulative effect are shown in figure 2.

In patients with Ezetimibe monotherapy because of a statin intolerance the net effect is calculated in the same manner as the patients with HIST end ezetimibe. The calculations will be performed for the total population and separately for patients with a history of ASCVD and DMII.

The results of the calculations will be presented in table 3.

The therapy during the first 12 weeks and the changes at one year follow-up will be presented in figure 3.

The cumulative effect in the first 12 weeks and at one year follow-up will be presented in figure 4.

The prevalence of drug-related adverse events and discontinuation rate of the lipid modifying drugs for the study population and subgroups (men and women,  $>70y$  and  $\leq 70y$ ) will be presented in a table. The intergroup analysis is performed using the Chi-squared test.

Prevalence of MACE is calculated as follows :  $\frac{\text{Patients with MACE at T52}}{\text{Total patients at T52}}$  The same calculation will be used for patients with decreased adherence for each treatment group (HIST, HIST+ezetimibe, HIST + Ezetimibe + PCSK-9i) and will be presented in table 3.

In the above mentioned analysis an LCL-c threshold of 1.8 mmol/l is used, the same analysis will be carried out using an LDL-c threshold of 1.4 mmol/L.

The percentage of patients with an LDL  $>1.8$  mmol/L and  $\leq 2.6$  mmol/L where a treatment with Alirocumab is started, will be calculated as follows:

$$\frac{\text{Patients with an LDL } > 1.8 \text{ mMol/L } \leq 2.6 \text{ mMol/L Alirocumab with}}{\text{Patients with an LDL } > 1.8 \text{ mMol/L } \leq 2.6 \text{ mMol/L on T8}}$$

[figure not shown]

Figure 2 Statistical analysis

On the left side: Different groups are labelled (A,B,C,...) based on the LDL-value and the different stages/steps.  
On the right side: The calculation of the net (Ntx) and cumulative (Ctx) effect for each step (T4,T8,T12) effect are shown. The net effect is the percentage of patients who reach the target (LDL-C ≤ 1.8 mMol/L) in the corresponding step. The cumulative effect is the percentage of all patients who reach the target (LDL-C ≤ 1.8 mMol/L) in the previous and the current steps  
For T0 the of calculation of the prevalence (Pt0) of patients with an LDL ≤ 1.8mMol/L is shown.

Table 3 Summary of the collected data

| Net effect of each consecutive step                               |                 |                 |                  |                            |
|-------------------------------------------------------------------|-----------------|-----------------|------------------|----------------------------|
|                                                                   | Pt 0 | Nt 4 | Nt 8  | Nt 12           |
| LDL≤ 1.8 mMol/L                                                   | n (%)           | n (%)           | n (%)            | n (%)                      |
| Cumulative effect of the consecutive steps                        |                 |                 |                  |                            |
|                                                                   | Pt 0 | Ct 4 | Ct 8  | Ct 12           |
| LDL≤ 1.8 mMol/L                                                   | n (%)           | n (%)           | n (%)            | n (%)                      |
| Prevalence of patients not reaching target at the different steps |                 |                 |                  |                            |
|                                                                   | T 0  | T 4  | T 8   | T 12            |
| LDL> 1.8 mMol/L                                                   | n (%)           | n (%)           | n (%)            | n (%)                      |
| One year follow up                                                |                 |                 |                  |                            |
|                                                                   | All patients    | HIST            | HIST + ezetimibe | HIST + Ezetimibe + PCSK-9i |
| LDL≤ 1.8 mMol/L                                                   | n (%)           | n (%)           | n (%)            | n (%)                      |
| ↓ Adherence                                                       | n (%)           | n (%)           | n (%)            | n (%)                      |
| MACE                                                              | n (%)           | n (%)           | n (%)            | n (%)                      |

HIST: High intensity statin therapy

[figure not shown]

Figure 3 Changes in therapy after one year

This figure is for illustration purposes only. The data of this illustration is fictional.

[figure not shown]

**Figure 4** *The cumulative effect of the consecutive steps*

*This figure is for illustration purposes only. The data of this illustration is fictional.*

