### **Data Handling Conventions For Patient Data**

Out of range data:

LDL-c  $< 0.5$  mmol/L and  $> 7.5$  mmol/L are double checked in the patients' medical record.

The following data will be considered as missing values in the calculation:

LDL-c  $> 20$  mmol/L

Missing data:

Missing values are handled using pairwise deletion. The case is excluded from the analysis if one or more data points needed for that particular calculation is missing.

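### Patients without a T52 LDL-C leave the one-year result but stay in the 12-week cumulative effect shown with it in Figure 4, so the two figures can differ because different patients are counted

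*SAP*

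**What the plan says.** The fourth secondary objective is "Prevalence of an LDL-C >1.8 mMol/L after 1 year of follow up". No denominator is written for it. The one-year block of Table 3 has an LDL-C row, given as a number and percentage for all patients and by treatment group, again without a denominator.

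The 12-week measure is defined in the Statistical analysis section: "The cumulative effect is the percentage of all patients who reach the target (LDL-C ≤ 1.8 mMol/L) in the previous and the current steps". It is then displayed together with the one-year result: "The cumulative effect in the first 12 weeks and at one year follow-up will be presented in figure 4".

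The section Data Handling Conventions For Patient Data sets the missing-data rule: "Missing values are handled using pairwise deletion", and "The case is excluded from the analysis if one or more data points needed for that particular calculation is missing".

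The only T52 denominator that the SAP writes out is the one for MACE, "Total patients at T52", and the same calculation is applied to adherence. Some patients will foreseeably have no T52 value, because the MACE definition itself ends with "revascularization and cardiovascular death) after 1 year". The SAP gives no rule for death or loss between T12 and T52, no same-patient display and no sensitivity analysis.

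**The concern.** The deletion rule works separately for each calculation. The one-year LDL-C result needs a T52 value. The 12-week cumulative effect does not, so a patient who reached target by T12 and later died, withdrew or gave no sample still counts there. A reader of Figure 4 will naturally take the step from week 12 to one year as a sign of whether control was kept, but part of that step may only reflect who was left to be measured.

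The one-year objective and Figure 4 are where the plan describes how far LDL-C control lasts. If patients who stop therapy or leave care are both less likely to be sampled and more likely to be above target, deletion would make lasting control look better than it is. It could even show a gain when no patient's status had changed.

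**Working it through.** **1. The plan's own figure.** From Sample size calculation: Z = 1.96, p = 0.20, d = 0.025. Then 1.96² × 0.2 × 0.8 / 0.025² = 983.4, which agrees with the stated 983. At the rounded-up 1000 patients the half-width is 1.96 × √(0.2 × 0.8 / 1000) = 2.48 points. This precision was set for the primary endpoint. It is not disputed and serves below only as a yardstick.

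**2. The rules applied to two patients.** One reaches target at T4 and is lost after T12. That patient is a success in the cumulative effect at T4, T8 and T12 and is absent from the one-year result. The other is above target at every step to T12 and is then lost. That patient is a non-success in the 12-week figure and is also absent at one year. Losing patients of the second kind raises one-year attainment relative to week 12; losing the first kind lowers it. Nothing in the SAP aligns the two sets of patients.

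**3. Effect on the one-year prevalence.** Let m be the share of patients alive at one year who have no T52 LDL-C, p the prevalence above target in those with a value, and p + g the prevalence in those without. Prevalence in all patients alive is

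(1 − m) × p + m × (p + g) = p + m × g,

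so deletion understates it by m × g, whatever the value of p. The SAP gives neither m nor g; both are assumed here.

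| m | g = 0 | g = 10 points | g = 30 points |
|---|---|---|---|
| 5% | 0 | 0.5 | 1.5 |
| 10% | 0 | 1.0 | 3.0 |
| 20% | 0 | 2.0 | 6.0 |

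**4. Limits without any assumption on g.** If 20% is reported among sampled patients (an assumed value) and m = 10%, the prevalence lies between 0.9 × 20% = 18% (all unsampled at target) and 18% + 10% = 28% (none at target). The upper limit is what a sensitivity analysis counting the unsampled as not at target would report. At m = 5% that result is 0.95 × 20% + 5% = 24%.

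**5. Effect on Figure 4.** Here the absent share L includes deaths, because they too leave the T52 set. Assume that no patient changes status after T12, that 8% of all patients are above target at T12, and that 20% of those later absent are. The 8% and 20% are illustrative and do not come from the SAP. The one-year figure among the remaining patients is (0.08 − L × 0.20) / (1 − L):

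- L = 5%: 0.07 / 0.95 = 7.37%, so attainment appears to rise from 92.0% to 92.6% (0.63 points).
- L = 10%: 0.06 / 0.90 = 6.67%, an apparent rise to 93.3% (1.33 points).
- L = 20%: 0.04 / 0.80 = 5.0%, an apparent rise to 95.0% (3.0 points).

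In general the artefact is L times the difference in 12-week attainment between patients who stay and patients who leave. Over L = 3% to 15% and a difference of 10 to 30 points it runs from 0.03 × 10 = 0.3 to 0.15 × 30 = 4.5 points. It is zero if the two groups do not differ, and zero by construction if both figures use the same patients.

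**The case against.** The strongest reply is that the analysis is declared descriptive, that no 12-week to one-year change is defined, and that the formulas and the display sit in Figures 2 and 4, which are not shown. All of that is true. A reader might infer that the SAP fixes a wrong denominator or plans a flawed test of change; the document supports neither. The T52 denominator is inferred from the deletion rule, and the written MACE denominator fits that inference. Still, prevalences are the study's main output, and the plan itself places the two results in one figure.

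A reader might also infer that the one-year result is certainly too favourable. The SAP does not support that: it gives no attrition rate and no information on the LDL-C of patients who leave. With no gap there is no bias, and at 3% to 5% loss it is small.

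A third objection is that deaths differ from lost samples. This stands. A patient who has died has no one-year LDL-C, and leaving that patient out of a one-year prevalence is defensible. Deaths matter here only because they change who is counted between the two figures.

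A fourth is that restricting the cumulative effect to patients with a T52 value would still compare having reached target by week 12 with being at target at one year. This also stands, and the fix must deal with it.

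Finally, Table 3 reports numbers with percentages, so denominators can be worked back and shrinkage noticed. That shows how many patients left, but not how well controlled they were.

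**Conclusion.** The point holds in a limited form. Followed as written, the deletion rule lets the 12-week and one-year results in Figure 4 rest on different patients, and the SAP has nothing to reveal or correct this. If patients alive but unsampled at T52 are worse controlled by an assumed 10 to 30 points, the one-year prevalence of unmet target is understated by 0.5 to 1.5 points at 5% missing and by 1 to 3 points at 10%. Only the upper end of the 10% case exceeds the 2.5-point margin, which in any case belongs to the primary endpoint. Direction and size rest on assumptions that the SAP can neither confirm nor exclude; the mismatch in who is counted follows from its rules. Confidence is moderate because the relevant figures are not shown. The change is worth making because it replaces a stated rule with a clearer analysis at little cost.

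**What to change.** In the Statistical analysis section, add that Figure 4 will show, beside the T52 result, the 12-week result again in patients with a T52 LDL-C. That repeat should use each patient's last LDL-C status in the first 12 weeks instead of having reached target at any step, and give the numbers moving from at target to above target and the reverse.

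For the one-year LDL-C objective and the one-year row of Table 3, state the denominator, the number of deaths and, separately, the number alive without a T52 LDL-C. Add one sensitivity result in which patients alive without a value count as not at target, next to the result in patients with a value.

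The cost is a few sentences, an extra table row and a little more analysis. LDL-C at each time point is already collected. Cardiovascular deaths come through MACE; other deaths would be taken from the SAE records listed under Study parameters collected, and the plan should confirm that these run to T52. The downside is that the sensitivity result will show a less favourable one-year figure.

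### The one-year MACE formula rests on an undefined T52 count which, read literally, drops cardiovascular deaths and some known events from a composite that includes them

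*SAP*

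**What the plan says.** Item h under Secondary Objective(s) defines the outcome as "Major adverse cardiovascular events (Myocardial infarction, stroke, (re-)hospitalization for cardiovascular diseases, revascularization and cardiovascular death) after 1 year".

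The Statistical analysis section gives its formula: the numerator is "Patients with MACE at T52" and the denominator is "Total patients at T52". Neither term is defined further. The same section divides the baseline prevalence differently, taking the patients above target "at baseline by the total included patients".

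Under Study parameters collected, MACE is listed at T52 only, while adverse and serious adverse events are recorded at every step. For missing data, Data Handling Conventions For Patient Data prescribes pairwise deletion: "The case is excluded from the analysis if one or more data points needed for that particular calculation is missing".

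Table 3 has a MACE row for all patients and for each of the three treatment groups. The SAP does not say when a patient is assigned to a treatment column or which events count there.

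**The concern.** The composite contains an event that, on a plain reading, takes the patient out of the composite's own denominator: someone who died of a cardiovascular cause in week 20 is not a patient at T52. A patient who had an infarction in week 6 and was lost in week 20 has no T52 record, so pairwise deletion can remove an event that is already known.

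The SAP has no rule for cardiovascular death, other death or loss to follow-up in this calculation. An analyst must choose, and the choices give different figures. A reader would take the result as the proportion of included patients with a MACE within a year, and the literal formula does not give that.

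**Working it through.** **The plan's own figure.** The SAP states no MACE rate, death rate or dropout rate. Its only computed figure is the sample size: 1.96² × 0.2 × 0.8 / 0.025² = 983.45, which reproduces the stated 983 but does not bear on this point.

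**Inputs.** N = 1000 included patients (from the SAP: "The number is rounded up to 1000 patients"). The rest are assumptions: D cardiovascular deaths, 20 to 60 (2–6%); F survivors with a non-fatal MACE, 100 or 150 (10% or 15% of those included); no other loss at first. N cancels, so the percentages do not depend on it.

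**Formulas.**
- All included: (D + F) / N
- Literal reading, deaths out of both terms: F / (N − D)
- Deaths in the numerator only: (D + F) / (N − D)

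| D | F | All included | Deaths out of both | Difference (points) | Numerator only | Difference (points) |
|---|---|---|---|---|---|---|
| 20 | 100 | 12.0% | 100/980 = 10.2% | −1.8 | 120/980 = 12.2% | +0.2 |
| 20 | 150 | 17.0% | 150/980 = 15.3% | −1.7 | 170/980 = 17.3% | +0.3 |
| 40 | 100 | 14.0% | 100/960 = 10.4% | −3.6 | 140/960 = 14.6% | +0.6 |
| 40 | 150 | 19.0% | 150/960 = 15.6% | −3.4 | 190/960 = 19.8% | +0.8 |
| 60 | 100 | 16.0% | 100/940 = 10.6% | −5.4 | 160/940 = 17.0% | +1.0 |
| 60 | 150 | 21.0% | 150/940 = 16.0% | −5.0 | 210/940 = 22.3% | +1.3 |

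**Second set of assumptions.** Fix total MACE at 10–20% of those included, with cardiovascular deaths of 1–5% counted inside it. Deaths out of both terms then understate MACE by 0.8 points (190/990 = 19.2% against 20%) to 4.7 points (50/950 = 5.3% against 10%). Deaths in the numerator only overstate it by 0.1 to 1.1 points.

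**Loss to follow-up.** This can move the ratio either way.
- Lost after a known MACE: starting from 120/1000 = 12.0%, dropping 10 such patients gives 110/990 = 11.1%.
- Lost without a MACE: with 200 MACE of which 10 are cardiovascular deaths, and 50 patients lost event-free, the literal ratio is 190/940 = 20.2% against 20.0%. Here the shrinking denominator slightly more than offsets the missing deaths.

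**Deaths kept in both terms.** If a cardiovascular death is recorded as a MACE at T52 and the patient stays in the denominator, such deaths cause no bias. The SAP does not state this rule.

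**The case against.** The strongest reply is that T52 may mean the one-year time point rather than attendance at a visit. Objective h covers the year, and MACE recorded at T52 has to look back over it, so a cardiovascular death could be entered as a MACE at T52 and remain in both terms. The SAP never expressly excludes the deceased. This much stands: a survivors-only rate is a consequence of the literal reading, not something the SAP declares. A reader might infer that reported MACE will certainly be biased downward. The documents do not support that, because a numerator-only reading biases it upward and event-free losses also push the ratio up. The reply still relies on a rule the SAP does not contain, and it does not recover events in patients lost before T52.

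It can also be said that adverse events are collected at each step, so an early MACE may be on file and need not count as missing. That is fair, and it makes the fix easier, but the formula does not say that such an event is used.

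A reader might further infer immortal time favouring the PCSK9-inhibitor column of Table 3, since a patient must reach about T8 to enter it. That does not fit the literal reading, under which every patient in every column survived to T52. The sentence extending the calculation to treatment groups concerns decreased adherence, and the SAP calls its analysis descriptive and plans no MACE comparison between columns. What remains is that neither the assignment time nor the event window for that row is given.

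**Conclusion.** The point holds as a defect in a stated formula. Followed literally, the formula omits the fatal component of a composite that includes it, and it can discard known events in patients lost early. Nothing else in the SAP repairs this.

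Under the first set of assumptions the literal ratio is 10.2–16.0% against 12–21%, an understatement of about 1.7–5.4 percentage points. This treats deaths as the only loss and rests on rates the SAP does not give. If deaths stay in the numerator only, the error is upward by about 0.2–1.3 points under the same inputs.

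This should be fixed. A reader might rate it as mandatory, but MACE is a descriptive secondary outcome, and the primary endpoint, the sample size and the planned chi-squared comparisons do not depend on it.

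**What to change.** Replace the formula in the Statistical analysis section. One-year MACE is the number of patients with at least one MACE from T0 to T52, counting cardiovascular death and any event recorded before loss to follow-up, divided by all included patients. Beside it, report how many patients were lost, and how many died of non-cardiovascular causes, without a prior MACE. A cumulative incidence with censoring at last contact is an optional alternative; it is a different estimator, so the SAP should name the one it uses.

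For the MACE row of Table 3, state the time at which patients are assigned to a treatment column and the window in which events count.

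The cost is a few lines of SAP text, plus MACE status for patients without a T52 visit, taken from the adverse-event data or the medical record; the optional estimate also needs event and last-contact dates. The reported figure will probably be somewhat higher. The simple proportion counts patients lost without an event as event-free, which is why their number must be shown.
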